We designed this study to use two forms of acupuncture. One form is basic acupuncture. This treatment for CFS is initiated from ‘*Science of Acupuncture and Moxibustion (9th edition, 2012)*’, a widely used textbook compiled by experts from 20 universities organised by the State Administration of Traditional Chinese Medicine (NATCM) in China [21]. Previous RCTs have proven the efficacy of basic acupuncture as a kind of baseline therapy [22–24]. In one study, the researcher reported an effective rate of 63.3%. Based on symptom evaluations, nine patients in the basic acupuncture group reported that their symptoms improved by more than two thirds compared with baseline symptoms. Ten patients reported that their symptoms were improved by a third. The 14-item Fatigue Scale (FS-14) also showed statistical significance via the paired- sample *t* test. The author considered this therapy mechanism for the regulation of liver and renal visceral functions, and as a benefit to the spleen *qi* [22]. Further, the chosen points, such as ST36, SP6, GV20, BL23, and CV4, were the top five acupoints selected for CFS based on a systematic review [20].

The other treatment is Jin’s three-needle acupuncture (JTN) treatment, a school of acupuncture treatment originating in South China. JTN has been widely used to improve sub-healthy conditions or treat diseases such as depression [25]. A previous RCT has noted that JTN treatment may improve somatic and mental fatigue in CFS patients. However, the sample size was small, and this study mainly recruited patients aged 18–30 years [22]. There is still a lack of RCTs for the study of JTN treatment on CFS.

We designed an RCT to compare basic acupuncture treatment and JTN treatment. The trial aims to identify the efficacy and safety of JTN treatment for CFS patients.

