### Sample size

The sample size was calculated via the effective rate based on the FS-14. In some previous acupuncture studies for CFS, researchers adopted the FS-14 score as one of the primary endpoints. The FS-14 score was applied with the formula:

$$ \left[\left(\mathrm{Value}\ \mathrm{pretreatment}-\mathrm{Value}\ \mathrm{posttreatment}\right)/\mathrm{Value}\ \mathrm{pretreatment}\times 100\%\right)\Big] $$

to calculate the effective rate [26]. Thus, based on this method and data from our preliminary study, we assumed the effective rate for the control group to be approximately 64% and the effective rate of JTN treatment to be approximately 86%. Therefore, based upon a two independent proportions power analysis conducted by an independent statistician via PASS 11.0, approximately 80 participants in each group will be needed to detect a statistically significant difference, with a significance level of 5% and a power of 90%. To allow for a predicted dropout rate of 15%, a sample size of 188 participants in total will be sufficient to detect a clinically important difference in this trial.

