### Data collection and statistical analysis

Acupuncturists will collect the data using Case Report Forms. Two independent researchers will then input the data into the database. All analyses will be carried out under the guidance of independent data monitors to ensure the safety and reliability of the data. For participants who drop out, we will record their number and the reason for termination, especially for adverse events.

All enrolled patients will be included in the primary analysis conducted in accordance with the intention-to-treat (ITT) principle. The data will be analyzed by SPSS for Windows version 19.0. The statistical significance is defined as a two-sided *P* value of ≤ 0.05. The baseline characteristics will be reported as the means ± standard deviation (SD). For comparison of baseline materials, a chi-squared or Fisher’s exact test will be used for categorical variables, Student’s *t* test will be used for normally distributed data and the Mann-Whitney *U* test will be used for non-normally distributed data. The scores of each rating scale and laboratory index before the intervention will be compared between the groups via Student’s *t* test or the Mann-Whitney *U* test. For the comparison within groups, the changes in the scores and indexes from baseline to endpoint will be assessed by a paired *t* test or the Wilcoxon rank-sum test. For the difference between groups, we will use Student’s *t* test or the Mann-Whitney *U* test. For the safety analysis, the adverse events will be listed and analyzed using a chi-squared or Fisher’s exact test. For participants who discontinue or deviate from intervention, listwise deletion or multiple imputation will be used.

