## Discussion

To our knowledge, this study is the first multicentre, single-blinded, and randomised acupuncture study applying JTN to treat CFS patients.

JTN is a kind of acupuncture therapy characterised by its special way of choosing treatment points. An acupuncture prescription is made up of one or more acupoint groups. Each group consists of acupoints that are influential points, empirical points, or local points. The combination of these points may generate an obvious curative effect compared with a normal mixture of ‘cookbook’ points. Thus, JTN offers the advantages of less acupoint selection with a distinct effect.

Based on the theory of traditional Chinese medicine, the points we chose are for energy balancing, which is necessary for improving the symptoms of CFS. Points such as PC6, ST36, SP6, and LR3 are regional distal points that act on an entire area to improve the state of energy imbalance from which the patient suffers. PC6, ST36, and the empirical point named the *Sishen* point also comprises a point group aimed at relieving fatigue. This group may help to tranquilise and free the body from tension. To prove the effect, we expect to gather related evidence via the assessment of the chosen scales and plasma indicators.

Notably, previous researchers have shown that HPA-axis dysfunction plays a major role in CFS development [40], and HPA-axis hypofunction may lead to inflammation/immune activation. It has been reported that the IL-2 and IFN-γ levels in CFS patients were increased compared to those in the non-fatigued controls [41], which may reflect a change in the Th1/pro-inflammatory immune response and NK cell function. Thus, the plasma ACTH, plasma cortisol, and serum levels of IL-2 and IFN-γ will be examined in this study to determine whether JTN treatment affects the immune and HPA functions of CFS patients.

One of the limitations of this study is that the patients were being followed up only at week 2. But we have trailed some of the patients at 4 weeks posttreatment by assessment of scales. The data of the 4-week follow-up will be collected for further analysis of the long-term effect of JTN.

In conclusion, the results of this study are expected to provide evidence on the efficacy and safety of JTN for CFS. Relevant plasma indicators will be measured to identify whether immune and HPA functions will be changed by acupuncture treatment.

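### The only between-arm analysis named for adverse events is a significance test with low power for uncommon events, so the safety aim needs estimates with confidence intervals

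*Protocol article*

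**What the plan says.** The Background names safety next to efficacy as the purpose of the study: "The trial aims to identify the efficacy and safety of JTN treatment for CFS patients". The Discussion repeats it: "the results of this study are expected to provide evidence on the efficacy and safety of JTN for CFS".

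The analysis is given under Data collection and statistical analysis: "For the safety analysis, the adverse events will be listed and analyzed using a chi-squared or Fisher’s exact test". The general criterion in the same section ("The statistical significance is defined as a two-sided" P value of at most 0.05) applies to that test. No other between-arm comparison of adverse events is named.

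The sample size rests on efficacy alone. Under Sample size, "we assumed the effective rate for the control group to be approximately 64% and the effective rate of JTN treatment to be approximately 86" per cent, "with a significance level of 5% and a power of 90" per cent. From this, "approximately 80 participants in each group will be needed to detect a statistically significant difference", and "To allow for a predicted dropout rate of 15%, a sample size of 188 participants in total will be sufficient". Nothing there refers to adverse events.

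The section on adverse events and safety monitoring adds descriptive evaluation and oversight. Events are assessed by frequency, severity and symptoms. Serious and unexpected events go to the Ethics Committee. All events are reviewed periodically, and a meeting can be called to weigh benefit against risk. The section lists the possible event types, from nausea and haematoma to injury of viscera or nerves, but gives no expected rates.

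**The concern.** A chi-squared or Fisher's test can return two answers: a difference was shown, or it was not. The second is informative about safety only if the test would probably have found an excess that matters. This trial was sized to separate 64% from 86%, a gap of 22 percentage points between fairly common outcomes. A doubling of an uncommon harm is a much smaller gap in absolute terms.

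The comparator is also acupuncture. Two needling arms could carry the same risk and still both carry a risk worth knowing, and a P value for their difference does not speak to that.

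At stake is what the report can say about one of the trial's two aims. With the test alone, a reader would not learn how large an excess of harm remains compatible with the data.

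**Working it through.** **1. The plan's own sample size.** Inputs from Sample size: 0.64 v 0.86, two-sided 5%, power 90%. With pooled variance (mean rate 0.75):

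n = [1.960 × √(2 × 0.75 × 0.25) + 1.282 × √(0.64 × 0.36 + 0.86 × 0.14)]² / 0.22²
= (1.200 + 0.759)² / 0.0484 ≈ 79.3, so 80 per arm.

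This agrees with the article; power at 80 per arm is 90.2%. For dropout, 80 / 0.85 = 94.1, which the article takes as 94 per arm, 188 in total. The efficacy figure is reproduced, and it is the only quantity for which the trial is sized.

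**2. Chance that the adverse-event test misses a doubling.** The article gives no rates, so the control-arm rate is an assumption, varied from 1% to 30%. The unit is assumed to be the participant with at least one event. For each pair of rates p and 2p, every pair of counts (i, j) from two independent binomials was enumerated:

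miss rate = 1 − Σ Pr(i) Pr(j) over all pairs with two-sided P ≤ 0.05.

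The chi-squared test is uncorrected.

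| Assumed rates, basic v JTN | Missed, 94 per arm (chi-squared / Fisher) | Missed, 80 per arm (chi-squared / Fisher) |
|---|---|---|
| 1% v 2% | 95% / 99.5% | 96% / 99.7% |
| 2% v 4% | 89% / 96% | 90% / 97% |
| 5% v 10% | 75% / 82% | 79% / 86% |
| 10% v 20% | 51% / 59% | 58% / 65% |
| 20% v 40% | 14% / 18% | 20% / 26% |
| 30% v 60% | 1% / 2% | 3% / 4% |

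For scale, 80% power for a doubling would need 435 per arm at 5% v 10% and 199 per arm at 10% v 20%.

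**3. What the test leaves unsaid.** These counts are illustrations, not predictions.

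- 10/94 v 5/94: Fisher P = 0.28. The difference is 10.6% − 5.3% = 5.3 points. The Wilson limits are 5.9% to 18.5% and 2.3% to 11.9%, so the Newcombe interval runs from 5.3 − √[(10.6 − 5.9)² + (11.9 − 5.3)²] to 5.3 + √[(18.5 − 10.6)² + (5.3 − 2.3)²]. With unrounded limits that is −2.8 to +13.7 points. The P value alone would hide that an excess of nearly 14 points is not excluded.
- 5/94 v 0/94: Fisher P = 0.059, so a harm seen five times in one arm and never in the other is still non-significant.
- 0/94 in one arm: the exact two-sided 95% upper limit is 1 − 0.025^(1/94) = 3.8%. Even with no events of a given type, absolute risk is bounded only at about 4%.

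**The case against.** Several points on the other side are fair.

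- A reader might infer that safety is judged by the test alone. The documents do not support this: events are also listed, and the adverse-events section provides for evaluation by frequency, severity and symptoms with continuing review. Listed counts with known denominators do give absolute rates. What remains is that neither the listing nor the oversight quantifies the excess still compatible with the data.
- A reader might also infer that a non-significant result will be declared safe. No section sets that rule or claims equal safety, and the aims are worded cautiously. Nothing in the Background or Discussion needs to be withdrawn.
- The miss rates depend on rates that the article does not give. If adverse events are common, as they might be over ten sessions with minor events counted, the test does reasonably well: a doubling from 20% to 40% is missed less than one time in five. The weakness is confined to uncommon events.
- Intervals may already stand in a full protocol or analysis plan that is not shown, and most efficacy trials are not powered for harms. So the absence of intervals is not in itself an error, and the test is valid for what it does. The point rests on what the article does name: a difference test that, used alone, suits the safety aim poorly when better information can be had from the same data.

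**Conclusion.** The point holds in a limited form. The only between-arm adverse-event analysis that the article names is a two-sided 5% test, in a trial sized for the FS-14 effective rate alone. Under assumed control rates of 5% to 10%, with 94 per arm, it would miss a doubling between about half and four-fifths of the time. It is weaker still for rarer events and adequate for common ones. For uncommon events a non-significant result is therefore not by itself evidence of safety, and with needling in both arms it leaves absolute risk unaddressed. All power figures rest on assumed rates and on counting participants, not episodes. This is a cheap improvement to analysis and reporting. It does not affect the primary result, the sample size or the monitoring of participants.

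**What to change.** In Data collection and statistical analysis, extend the safety sentence to say that:

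- for each arm, the proportion of participants with at least one adverse event, overall and for each event type listed in the adverse-events section, will be reported with an exact 95% confidence interval;
- the JTN-minus-basic risk difference will be reported with a 95% confidence interval, for example Newcombe's;
- the safety statement will be based on these intervals, the chi-squared or Fisher P value will be descriptive, and P > 0.05 will not be taken as evidence of safety.

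If the full plan already contains such intervals, it is enough to bring this sentence into line with it. The Background and Discussion need no edit.

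The cost is a few lines of text and of the safety table, from data already collected and with no further participants. The downside is a more guarded safety claim.

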### Concomitant treatments

The patients in the two groups will be discouraged from any additional specific complementary treatments related to CFS throughout the trial, including moxibustion, herbal medicine, massage, etc. If a patient needs medications, such as antidepressant drugs and anxiolytics, or to undertake mind-cure, then the relevant information will be recorded in the Case Report Form for that patient. Two researchers, blinded to the treatment, will assess whether to adopt the data.

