### Outcome measures

As the CFS diagnostic criteria are mainly based on the patient’s symptoms, we considered symptom improvement as the primary outcome. Thus, the patient-reported outcome (PRO) method was adopted in this trial. The primary outcome was the effective rate based on the FS-14 score. The FS-14, which is used to evaluate the fatigue level of the patient, reflects the severity of fatigue from two different angles: physical fatigue and mental fatigue [29, 30]. A higher score suggests more serious fatigue. The FS-14 score will be applied with a formula, namely:

$$ \left[\left(\mathrm{Value}\ \mathrm{pretreatment}-\mathrm{Value}\ \mathrm{posttreatment}\right)/\mathrm{Value}\ \mathrm{pretreatment}\times 100\%\right] $$

to calculate the effective rate. If the integral is reduced by ≥ 60% after treatment, then the treatment will be marked as a notable effective. If the integral is reduced by < 60% but ≥ 30%, then the treatment will be considered as effective. If the integral is reduced by < 30%, then the treatment will be regarded as ineffective [26].

The secondary outcomes include the Fatigue Assessment Scale (FAI), Depression Status Inventory (DSI), and Self-rating Anxiety Scale (SAS): (1) The FAI, a 29-item scale, with scores ranging from 1 to 7 for each choice, evaluates four dimensions of fatigue: fatigue severity (11 items), the sensitivity of fatigue under particular circumstances (six items), associated consequences of fatigue (three items), and the response to sleep (two items). A higher score indicates greater problems with fatigue [31, 32]; (2) The DSI, consisting of 20 questions, is used to evaluate the depressive state of the patient in the past week. This assessment reflects the emotional, somatic, psychomotor retardation, and mental disorders of depression. The DSI is especially suitable for general hospitals to find patients with depression [33]; and (3) The SAS, containing 20 questions, is used to evaluate the level of anxiety of a patient at 1 or 2 weeks before taking the test. The assessment is based on scoring in four groups of manifestations: cognitive, autonomic, motor, and central nervous system symptoms [34].With scores ranging from 1 to 4, a higher SAS or DSI score indicates a higher risk of developing anxiety and depression.

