### Adverse events and safety monitoring

Adverse events will be recorded and managed by researchers within 24 h. There will be at least one physician to evaluate and manage the adverse events at each centre. Serious adverse and unexpected events will be reported to the Ethics Committee and other supervising departments. The subjects may leave the trial at their own discretion, or the physicians will determine whether the patient will continue or terminate the study. However, the patient will be followed up until they are in a stable condition following the adverse event.

The primary investigator will review all adverse events periodically, and the Ethics Committee and DMC will have access to the interim results. If necessary, a meeting will be held to reappraise the benefits and risk of this trial.

The possible adverse events related to acupuncture treatment include fainting during acupuncture treatment, nausea, haematoma formation, local infection, injury to the viscera or the peripheral nerves, stuck needle, and needle breakage. Adverse events will be evaluated based on the frequency, severity and symptoms of the patients throughout the trials. Patients who are intolerant to the acupuncture treatment should be removed from the trial.

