### Blinding

The participants will be blinded in this trial. The coordinator will send the study number and group allocation to the acupuncturist via Email. The records of the acupuncturist will be stored in a locked briefcase that will only be available for the acupuncturists and cooperative researchers. Only the acupuncturists and the coordinators will know the group allocation of each participant. The researchers and acupuncturists must not discuss related information with the participants. As patients in the two groups will adopt different positions, these individuals will not be treated in the same place after randomisation. Acupuncturists will inform the patients about the location of the treatment rooms prior to each treatment session. Therefore, the chance of acquaintance between patients in the two groups will be reduced as much as possible.

Unblinding is permissible when a participant leaves the trial at their own discretion or the physicians determine that they should terminate the trial. The blinding will be monitored and assessed by independent statisticians responsible for data monitoring and by the Ethics Committee of the study centre. After receiving permission from the supervisors, the acupuncturists may reveal the allocated intervention to the patient who dropped out.

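### The plan promises that all enrolled patients enter an ITT primary analysis, yet permits exclusion after randomisation by two routes, neither with a stated rule

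*Protocol article*

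**What the plan says.** All places are in the Protocol article.

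- **Data collection and statistical analysis**, on who is analysed: "All enrolled patients will be included in the primary analysis conducted in accordance with the intention-to-treat (ITT) principle".
- **The same section**, closing sentence: "For participants who discontinue or deviate from intervention, listwise deletion or multiple imputation will be used".
- **Concomitant treatments.** The trigger is a need for other treatment during the trial: "If a patient needs medications, such as antidepressant drugs and anxiolytics, or to undertake mind-cure". This is recorded, and then: "Two researchers, blinded to the treatment, will assess whether to adopt the data". No criterion follows.
- **Adverse events and safety monitoring**: "Patients who are intolerant to the acupuncture treatment should be removed from the trial". The sentence does not separate stopping the needling from stopping outcome collection.
- **Outcome measures**: "The primary outcome was the effective rate based on the FS-14 score". The rate is a responder proportion from a self-reported scale, measured before and immediately after treatment.

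**The concern.** The first two statements cannot both govern the primary analysis. If listwise deletion is used, not every enrolled patient is analysed. Three features make this more than loose drafting.

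1. **The trigger is treatment status.** Missing sessions or departing from the assigned treatment is not the same as lacking a post-treatment FS-14. As written, someone with an observed score could be excluded.
2. **The method is left open.** Deletion and imputation are offered as alternatives with no rule for choosing, and the article does not say that the choice is made before the data are seen.
3. **There is a second exit.** Data may be set aside because a patient needed an antidepressant, an anxiolytic or psychological treatment. That need arises after randomisation. It is plausibly linked to fatigue, depression and anxiety, which are what the trial measures.

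At stake is the protection that randomisation gives the primary comparison. If those excluded respond less often than the rest, and the arms lose different numbers of them, the arm that loses more gains an apparent advantage.

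**Working it through.** **Step 1: the plan's own figure.** Inputs from Sample size: 64% versus 86%, significance level 5%, power 90%. The statistical section makes the test two-sided. With a pooled rate of 0.75:

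n = [1.960 × √(2 × 0.75 × 0.25) + 1.282 × √(0.64 × 0.36 + 0.86 × 0.14)]² / 0.22² = (1.200 + 0.759)² / 0.0484 = 79.3, so 80 per arm.

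Allowing for 15% dropout, 160 / 0.85 = 188.2, stated as 188, or 94 per arm. The figure reproduces. The inflation leaves 94 × 0.85 ≈ 80 analysable per arm, so up to 14 per arm are expected to be lost.

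**Step 2: can the handling decide significance?** Assumed data: 14 lost in each arm, with 63 and 51 responders among the 80 remaining (Pearson chi-squared, no continuity correction).

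- Deletion: 63/80 = 78.8% versus 51/80 = 63.8%; z = 0.150 / 0.0716 = 2.10, p = 0.036.
- Lost participants kept as ineffective: 63/94 = 67.0% versus 51/94 = 54.3%; z = 0.128 / 0.0713 = 1.79, p = 0.073.

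The second rule is not one of the plan's two options. The example shows only that the treatment of these participants can move a result across the 5% line.

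**Step 3: type I error under deletion.** Assume a true rate p = 0.64 in both arms and 94 per arm. If a fraction d of an arm is deleted and the deleted respond at rate q, the rate among those kept is (p − d·q)/(1 − d). The shift is the false difference divided by its standard error, and

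type I error = Φ(shift − 1.960) + Φ(−shift − 1.960).

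Worked for 20% of JTN and 10% of control, with q = 0:

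- Kept rates: 0.64/0.80 = 80.0% and 0.64/0.90 = 71.1%, a false difference of 8.9 points.
- SE = √(0.800 × 0.200/75.2 + 0.711 × 0.289/84.6) = 0.0675.
- Shift = 0.0889/0.0675 = 1.317, so Φ(−0.643) + Φ(−3.277) = 26%.

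| Deleted, JTN / control | Response among deleted | Kept rates | False difference | Type I error |
|---|---|---|---|---|
| 15% / 15% | same in both arms | equal | 0 | 5% |
| 9 / 5 | none | 70.8% / 67.6% | 3.2 points | 7.4% |
| 20% / 10% | 32% | 72.0% / 67.6% | 4.4 points | 9.4% |
| 20% / 10% | none | 80.0% / 71.1% | 8.9 points | 26% |
| 14 / 0 | none | 75.2% / 64.0% | 11.2 points | 37% (exact 36.5%) |

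Here 94 × 0.64 = 60.16 responders, giving 60.16/85, 60.16/89 and 60.16/80 for the rows stated as counts.

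The table treats those kept as a binomial sample at the kept rate. If instead an exact number of non-responders is struck from each arm while responder counts vary around 64%, the 9 / 5 row becomes 9.7%. Striking 7 or 14 from each arm gives 7.1% or 10.8%, split evenly between directions: precision is overstated but neither arm is favoured. Exchanging the arms reverses the sign of every difference.

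**The case against.** Several points on the other side are sound.

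- **Deletion is permitted, not required.** Multiple imputation is the alternative, and imputing missing outcomes is compatible with ITT. This stands. What remains is that the choice is open and one of the two options contradicts the ITT sentence.
- **The sentence may be a loosely worded missing-data rule.** Both methods are standard tools for missing data. A reader might infer that observed FS-14 scores would be overwritten by imputed ones. The text does not say so. It supports only that participants with an observed score could be excluded, because departing from treatment is itself named as a trigger.
- **The researchers who decide on adopting data are blinded**, and analyses run under independent data monitors. Both limit deliberate selection by arm. They do not restore ITT, since an exclusion made blind is still informative if the triggering event depends on arm and response.
- **The large figures are extreme.** The plan predicts 15% dropout with no split by arm. The 36% case assumes that every loss is a JTN non-responder and that control loses nobody. This stands, so a range is the fair statement.
- **Unblinding.** The Blinding section says: "Unblinding is permissible when a participant leaves the trial at their own discretion". A reader might infer that leavers learn their arm before giving the post-treatment FS-14. The section requires supervisors' permission, concerns patients who have already dropped out, and does not place disclosure before any score. That is an inference about timing and no part of this point.
- **An SAP could settle it.** An SAP may supply an imputation model or a list of sensitivity analyses, and their absence here is no fault. It should not have to resolve two incompatible statements about who is in the primary analysis.

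**Conclusion.** The point holds as an internal inconsistency in the statistical section, together with an exclusion route in the section on concomitant treatments that has no criterion. Followed as written, these rules can give a biased primary comparison.

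The likely size is unknown. In the assumed scenarios, type I error runs from about 5%, when the amount of loss and the response among the lost are alike across arms, through 7% to 10% and 26%, to about 36% at the extreme. Only the 64%, 86%, 15%, 80 and 188 come from the article. The splits by arm, the response among those lost and the use of Pearson chi-squared are assumptions. The direction could favour JTN or basic acupuncture.

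It would go too far to say that the plan does delete everyone who stops, or that it will produce a false positive. It allows deletion, and nothing in it prevents unequal, response-related loss. Because the defect governs who enters the primary analysis, it should be settled before any outcome is analysed by arm.

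**What to change.** 1. **Primary analysis set.** State that the primary analysis includes all randomised participants in their allocated arm and uses every observed post-treatment FS-14, whatever the deviation or concomitant treatment.
2. **One method for missing outcomes.** Name multiple imputation as the single primary method, applied only where FS-14 is missing. The imputation model can be left to the SAP.
3. **Adoption of data.** Replace the blinded case-by-case decision with a per-protocol sensitivity analysis whose criteria are fixed before unblinding.
4. **Outcome collection.** Seek the post-treatment scales, with continuing consent, from those who stop treatment. Reconcile the sentence on removing intolerant patients with the ITT statement, so that stopping treatment is distinguished from ending data collection. No clinical decision to stop treatment changes.

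**Cost.** A wording amendment, possibly through the three review boards that approved the protocol, and a little imputation work. The trial is already recruiting, so scores from participants already removed may not be recoverable. Their number should be reported by arm.
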